### Secondary Outcomes

- a. Changes biomarkers (TBD)
- a. Changes in small artery elasticity (SAE)

## **2.3. Design Justification**

### General Design:

A randomized trial design will control for both known and unknown confounders, and the 2X2 factorial design will allow separate evaluation of the treatment interventions. Visit frequency was chosen to evaluate short-term tolerability and risk factor changes in an efficient manner with this initial pilot phase. Other CVD risk factors, such as smoking, will not specifically be targeted in the context of study visits so as not to confound the effect of pravastatin and/or lisinopril.

### Targeted Study Population:

The purpose of this study is to study two components of a polypill (statin and ACEi) among HIV-infected participants who are at least at moderate CVD risk by traditional risk factor assessment. Both HIV-infection and ART increase CVD risk further, so the Framingham risk score cut-off for inclusion was low-moderate (see below). Primary prevention for CVD is more appropriate for patients at low risk for AIDS events, and, thus, we included only HIV-infected participants receiving effective ART.

### CVD Risk Threshold (use of Framingham Risk Score):

Traditional CVD risk algorithms, such as Framingham, remain generally effective at predicting risk among HIV-infected patients. The National Cholesterol Education Program Adult Treatment Panel III (ATP III)

designates CVD risk, based on traditional risk factors (smoking, BP $\geq$ 140/90, HDLc <40mg/dL, family history of premature CVD and age  $\geq$ 45 years for men and  $\geq$ 55 years for women) and Framingham 10 year risk score (FRS), into 4 categories: 1) Lower risk is 0-1 risk factor and FRS <10; 2) Moderate risk is 2+ risk factors and FRS <10; 3) Moderately high risk is 2+ risk factors and FRS of 10-20; and 4) High risk is CVD or CVD equivalent, which may include a FRS >20.

We attempted to targeted HIV infected patients of at least moderate CVD risk, as the very lowest risk patients are less likely to benefit from primary prevention and BP and/or lipid-lowering therapy. Use of Framingham risk score for inclusion criteria allows consideration of age, gender, systolic BP, TC, HDLc and smoking status. ART exposure and HIV infection could also both be considered to increase CVD risk (see background). A Framingham risk score cutoff of  $\geq$ 3% eliminates the participants at very low risk for CVD. Most recent estimates from the D:A:D (Data Collection on Adverse Events of Anti-HIV Drugs) study indicate risk for myocardial infarction increases 16% with each additional year of ART exposure. Applying these data, an HIV-infected patient with approximately 4 years of ART exposure, and a Framingham risk score of 3%, will have 10-year risk of CVD event of approximately 5%. This estimate does not account for increased risk of CVD associated with HIV infection itself. The use of a the Framingham 10-year risk score as a screening tool for this study was also motivated by the ease of implementing this strategy in clinical practice.

#### Study Drug:

The choice of drugs for this study was motivated by their efficacy as secondary prevention for CVD events, adjunct anti-inflammatory properties, availability as generic preparations, and potential to counter HIV- and ART-specific CVD risk mechanisms beyond BP and lipid lowering properties. In addition, some statin medications are contraindicated when taking PIs (due to interactions with CYP3A4 pathway), and for this reason pravastatin is the preferred given a lack of metabolism through the CYP3A4 pathway. Darunavir has been noted to increase pravastatin levels to a greater extent than other PIs, and participants taking darunavir will be counseled specifically about this but will not be excluded from participating for this reason.

Both pravastatin and lisinopril are available in generic form. These drugs also have a long track record of being used safely in a clinical setting. Participants for whom BP or cholesterol treatment is indicated will not be enrolled. In addition to clinical monitoring for side effects, toxicity labs will be included at study visit. A clinical doctor of pharmacy (PharmD) is included on the protocol team and will review each participant's medication list upon enrollment. If toxicity to study drugs develop, then participants will be un-blinded and discontinue any active study medication per monitoring criteria below.

## **2.4. Data Collection**

Details of study will be reviewed with all interested participants. If inclusion criteria are likely based on review of clinic records then a screening visit may be scheduled, where labs and BP will be assessed. Informed consent will be obtained at screening visits. Screening blood draw results will be used to verify blood lipid eligibility criteria (LDLc and TG). The lowest BP reading, taken from up to 3 readings during a screening visit, may be used to assess eligibility criteria. Participants will be given an information pamphlet on ways to reduce heart disease risk at enrollment. If exclusion or withdrawal criteria are met due to BP or lipid level thresholds, then a note with these results will be sent to the participants primary care giver with recommendations that they be evaluated for hypertension or dyslipidemia, respectively.

If eligibility criteria are met, participants will be randomized at the baseline visit to occur within 2 months of screening/consent. After enrollment and baseline visit, participants will present month 1 and month 4 for repeat study procedures. The visit schedule is outlined in the table below. Visits will last approximately 60 minutes.

Toxicity labs and a clinical assessment will be scheduled at any point during the 4 months follow-up if new symptoms develop that may be related to study medications. Toxicity labs and adherence will otherwise be assessed along with study procedures at scheduled 1 and 4 month visits.

**TABLE:** Study procedures and visit timeline

| Measure                      | Screening visit            | Baseline visit       | Symptoms? | Month 1 visit | Month 4 visit |
|------------------------------|----------------------------|----------------------|-----------|---------------|---------------|
| Informed consent             | X                          |                      |           |               |               |
| Randomization                |                            | X                    |           |               |               |
| BP                           | X                          | X                    |           | X             | X             |
| Lipids (TC, HDLc, LDLc, TG)  | X                          | X (if not at screen) |           | X             | X             |
| FRS                          | X                          | X                    |           | X             | X             |
| Med Adherence                |                            |                      | X         | X             | X             |
| Hep B/C serologies           | X                          | X (if not at screen) |           |               |               |
| Toxicity labs (CMP, CBC, CK) | X                          | X (if not at screen) | X         | X             | X             |
| HIV labs (RNA, CD4)          | X (if not $\leq 3$ months) | X (if not at screen) |           | X             | X             |
| Artery Elasticity            |                            | X                    |           | X             | X             |
| Biomarkers                   |                            | X                    |           | X             | X             |
| Stored Specimens             |                            | X                    |           | X             | X             |

Randomization will be predetermined using block-randomization with varied groups of 4 and 8, and blinded to investigators, staff and participants. An un-blinded statistician, one research staff not involved with study visits, and an HCMC pharmacist will have access to the randomization code.

Pravastatin and lisinopril will be purchased through HCMC pharmacy at reduced generic pricing. Active study drugs and placebo pills will be encapsulated (Custom-Rx Compounding Pharmacy in Richfield, MN) and then packaged and labeled with a study identification number. Study medications will be stored and dispensed by study investigators. Investigators will comply with HCMC policies on use of medications for ongoing IRB approved studies.

## 2.5. Sample Size Considerations

With a total sample size of 40 patients (20 per group for comparison of each drug intervention), a  $0.9 \times SD$  (standard deviation) difference in 10-year Framingham risk score from each drug can be detected with 80% power at the 0.05 (2-sided) level of significance. The variability in Framingham risk score was estimated from the Multiple Risk Factor Intervention Trial (MRFIT), where the estimated SD based on 11,702 participants was 0.20, corresponding to a relative change of approximately 20%. Thus, a  $0.9 \times SD$  change in this pilot study would correspond to an 18% relative change in Framingham risk score over the follow up period. Thus a change in Framingham risk of 8% to 6.5% would be  $>18\%$  relative improvement. In this proposal, if a 40-year old male smoker with SPB of 130mmHg, TC of 190mg/dL,

HDLc 35mg/dL demonstrated a reduction in SBP of -5mmHg and TC of -20mg/dL, and no increase in HDLc, his 10-year Framingham risk score would have a 25% relative improvement (8% to 5%). This is a very reasonable estimate as a mean change in TC of -40mg/dL after 12 weeks of pravastatin treatment was reported among 86 HIV-infected participants, and patients in our HCMC clinic commonly have lipid profiles less favorable than this.

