## **2.2. Outcomes**

### Primary Outcomes

- a. Medication tolerability
  - i. Study withdrawal due to medication side effect (subjective or lab criteria)
  - ii. Discontinuation of a single study medication due to side effect (subjective or lab criteria)
  - iii. Lab measure with  $> 2$  fold increase (with emphasis on: Creatinine, CK, AST, ALT)
- b. Adherence to study medication
  - i. Self report of misses per week
  - ii. Pill count by study RN – reported as % (pills taken/days enrolled in study)
- c. Changes in Framingham risk score (FRS), including serum cholesterol levels and blood pressure

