## 4. ANALYSIS PLAN

The general goal of this pilot study is to gather feasibility and efficacy data, utilizing a 2x2 factorial design (4 cells of  $n=10$ ,  $n=40$  total), to inform planning for a multi-center HIV/CVD polypill trial. We believe treatment with pravastatin (20mg daily) and lisinopril (10mg daily) will be well tolerated and be well adhered to by participants engaged in care and already adherent to ART. We hypothesize that Framingham risk score will improve with either drug intervention. Future sample size estimates will be generated from effect size related to changes in arterial elasticity and biomarkers.

**Primary Analyses:** Mean changes in FRS after 4 months will be studied with pravastatin use (versus placebo) and lisinopril use (versus placebo). The effect of both drugs combined, compared with double-placebo, will also be examined. Adherence and the frequency of intolerability, based on subjective or lab criteria, will also be compared between groups using the definitions listed in ‘outcomes’ (2.2). Elevations in lab values will also be categorized by severity (using established grades 1-4).

**Secondary Analyses:** Mean changes in hsCRP, IL-6, D-dimer, SAE, ApoB, ApoA1, and LDL and HDL particle concentrations will be studied after 4 months of pravastatin and lisinopril, given alone or in combination, using similar methods as above in primary analyses. Tests for correlation between change in these markers and BP, total cholesterol and FRS will also be considered. Regression models may be

considered to adjust for additional clinical characteristics (including, but not limited to traditional CVD risk factors), but power will be quite limited for these analyses.

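### Section 2.5 claims 80% power for an 18% relative change in Framingham risk score (FRS), but section 4 does not commit to the relative scale; a comparison in FRS points would have about 67–71% power under assumed baselines

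*Combined protocol and SAP*

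**What the plan says.** Section 2.5 (Sample Size Considerations) assumes 40 participants, "20 per group for comparison of each drug intervention", and says that a difference of 0.9 SD "can be detected with 80% power at the 0.05 (2-sided) level of significance". The SD comes from a large prevention trial, "where the estimated SD based on 11,702 participants was 0.20, corresponding to a relative change of approximately 20" per cent. The detectable effect therefore "would correspond to an 18% relative change in Framingham risk score over the follow up period". Both illustrations that follow are also given as relative improvements.

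Section 2.2 lists the outcome as "Changes in Framingham risk score (FRS), including serum cholesterol levels and blood pressure". Section 4 gives the primary analysis as "Mean changes in FRS after 4 months will be studied", for each drug against its placebo. Neither section says whether change means percentage points of FRS, percent of baseline or log FRS. Neither names a test, a baseline covariate or a term for the other drug.

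For the secondary outcomes, section 4 says "Mean changes in hsCRP, IL-6, D-dimer, SAE, ApoB, ApoA1, and LDL and HDL particle concentrations will be studied after 4 months", by methods similar to the primary analysis and with no transformation stated. It adds that future sample sizes will rest on the effects seen for arterial elasticity and biomarkers.

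**The concern.** FRS is itself a percentage, so a mean change in it is easily computed in points. Section 2.1 admits participants with FRS of at least 3% and excludes those above 20%. The same 18% relative fall is then 0.18 × 3 = 0.54 points at the bottom of the range and 0.18 × 20 = 3.6 points at the top. If variation is roughly proportional to baseline, as an SD quoted in relative terms suggests, high-risk participants contribute most to both the mean and the variance in points. The power claimed in section 2.5 would not carry over to that analysis.

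The factorial layout adds a second issue. Half of each comparison group also takes the other drug, and section 4 hypothesises that either drug improves FRS. Without a term for the other drug, its effect enters the residual variance.

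At stake are the power of the FRS comparison, a choice of scale left open until data are seen, and the form of the biomarker estimates passed to the next trial.

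**Working it through.** **Inputs from the documents.** n = 20 per group, two-sided 0.05, difference 0.9 SD, SD 0.20 on a relative scale (section 2.5); baseline FRS 3–20% (section 2.1); four cells of 10 (section 4).

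**Assumptions.** Relative change is independent of baseline. The baseline distribution is not given, so several within 3–20% were tried. The documents do not say whether 0.20 is an SD of log FRS or of proportional change; both were considered.

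**1. The plan's own figure.** n per group = 2 × [(1.96 + 0.842)/0.9]² = 19.4, rounded up to 20. Power at 0.18/0.20 = 0.9 SD is 81.2% (normal) or 79.2% (noncentral t, 38 df). The stated 80% reproduces.

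**2. Points, other drug inert.** Change in points = baseline × relative change. With CV the coefficient of variation of baseline FRS, and effects in units of mean baseline:

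- v_drug = (1 + CV²)(0.18² + 0.20²) − 0.18²
- v_placebo = (1 + CV²)(0.20²)
- effective d = 0.18 / √[(v_drug + v_placebo)/2]

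At CV 0.5: v_drug = 1.25 × 0.0724 − 0.0324 = 0.0581; v_placebo = 0.0500; d = 0.18/√0.05405 = 0.774; power 66.5% (t).

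| Baseline CV | d | Power (t) |
|---|---|---|
| 0 | 0.900 | 79.2% |
| 0.3 | 0.848 | 74.3% |
| 0.4 | 0.813 | 70.8% |
| 0.5 | 0.774 | 66.5% |

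**3. Simulation.** 20,000 trials per setting, log-change SD 0.20; baselines uniform, log-uniform or truncated log-normal within 3–20%, CV 0.43–0.53. A log effect of 0.18 is 0.9 SD but only a 1 − exp(−0.18) = 16.5% fall. A true 18% fall is −ln(0.82) = 0.198 log units, or 0.99 SD. Both are shown, with the other drug inert:

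| Effect | Log scale | Points |
|---|---|---|
| 0.18 log units (0.9 SD) | 79% | 67–71% |
| True 18% fall (0.99 SD) | 86–87% | 75–78% |

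Runs differ by about one percentage point. Percent change from baseline gives about 78% in the first row. With a narrower baseline (CV 0.30), points give about 75% in the first row and 83% in the second.

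**4. Both drugs work equally, 0.9 SD each.** An unmodelled second drug adds 0.18²/4 = 0.0081 to a variance of 0.0400 on the log scale.

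| Comparison | Log scale | Points |
|---|---|---|
| Unadjusted | 73% | 55–60% |
| Adjusted for the other drug | 79% | 60–65% |

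**5. Fewer completers (assumed 10% or 20% loss).**

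| Per group | Power at 0.9 SD | Detectable at 80% | × 0.20 |
|---|---|---|---|
| 20 | 79.2% | 0.909 SD | 18.2% |
| 18 | 74.6% | 0.961 SD | 19.2% |
| 16 | 69.3% | 1.024 SD | 20.5% |

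**The case against.** The strongest reply is that the documents never mention points. Section 2.5 is the only place that defines a scale, and it is relative. Read with it, the mean changes of section 4 could well be percent changes, which keep about 78% power. This stands: a reader might infer that the plan specifies a comparison in points, but what it does is leave the scale open.

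A reader might also infer that power is really as low as 55%. That figure needs a second active drug left out of the model, and this also cuts log-scale power, to 73%. It therefore mixes scale with non-adjustment. With the other drug inert, 55% would need a baseline CV of about 0.73–0.8, above every distribution tried.

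If 0.20 is a log SD and the effect a true 18% fall, points retain 75–78%, close to the claim, and a narrow baseline spread removes the shortfall. If the SD in points were constant across baseline, these figures would not apply.

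It is also tempting to say that the biomarkers have the same problem. They do not: no biomarker power is stated, so nothing is contradicted. The documents do not describe the markers' distributions either. They only express hsCRP, IL-6 and D-dimer differences proportionally (50–100% higher than in general cohorts; a 37% hsCRP reduction with a statin that is not a study drug).

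On loss to follow-up, section 2.1 allows more than 40 participants, and stopping one study drug need not mean a missing month-4 FRS. The gap between 0.90 and 0.91 SD is rounding.

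**Conclusion.** The point holds as a gap in specification. The sample-size arithmetic is sound on the relative scale, but section 4 does not commit to that scale. Under the assumptions shown (relative change independent of baseline, baseline CV 0.43–0.53, other drug inert), analysing points costs about 8–12 percentage points of power: 67–71% against 79% at 0.9 SD, or 75–78% against 86–87% for a true 18% fall. If both drugs work, omitting the other drug costs about 6 further points on the log scale (79% to 73%), which adjustment recovers. The log scale had the higher power in every setting with the stated spread of baseline risk; the size of the gap depends on that spread, which the plan does not give.

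For the biomarkers, stating a transformation is an improvement and not the repair of a contradiction. It matters because their estimates are meant to size the next trial; section 4 does not give FRS that role. The missing allowance for loss is secondary.

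**What to change.** **Section 4, primary analysis.** Analyse log(month-4 FRS) with randomised drug, log(baseline FRS) and the other drug in the model. Report percent change with 95% CI, with percentage points as descriptive support.

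**Section 4, secondary analysis.** Use the same baseline-adjusted log model, reported as geometric mean ratios, for right-skewed markers such as hsCRP, IL-6 and D-dimer.

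**Section 2.5.** State that the 80% applies to the log (relative) scale with 40 completers, and that the detectable difference is about 0.96–1.02 SD with an assumed 10–20% loss.

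**Cost.** A few sentences and no new data, since baseline and month-4 values are already scheduled. The two covariates use two degrees of freedom (38 to 36), which moves power at 0.9 SD only from 79.2% to 79.1%. The stated detectable difference becomes slightly less favourable.

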## 2.6. Study procedures

At study visits participants will be assessed for study medication tolerability and toxicity, undergo a peripheral blood draw, and BP and artery elasticity measurements. Demographic characteristics, past medical history and additional risk factors will also be ascertained. Framingham 10-year risk score will be calculated using an NHLBI online algorithm (<http://hp2010.nhlbi.nih.net/atpiiii/calculator.asp>), after entering age, gender, smoking status, TC, HDLc, systolic BP and use of a BP lowering medication.

Medication tolerability: At each visit, subjective symptoms will be assessed along with toxicity labs will be assessed at each visit. Clinical assessment and toxicity labs will also be measured outside the context of study visits if participants develop subjective side effects that may be related to study medications.

Toxicity labs include:

- i. Complete blood count (CBC)
- ii. Complete metabolic panel (CMP: including liver function tests)
- iii. Creatine phosphokinase (CK).

Adherence: Adherence will be assessed via participant report and pill count (by study RN) during follow-up visits.

Arterial Elasticity Measurements: Arterial elasticity will be assessed via pulse waveform analysis (model PulseWave CR-2000, Hypertension Diagnostics, Inc., Eagan, MN), which provides the following measurements: large and small artery elasticity index (ml/mmHg; LAE and SAE respectively), systemic vascular resistance ( $\text{dyne} \cdot \text{sec} \cdot \text{cm}^{-5}$ ), total vascular impedance ( $\text{dyne} \cdot \text{sec} \cdot \text{cm}^{-5}$ ), cardiac output (L/min), pulse rate (beats/min), and BP (mmHg). Measures will be assessed in triplicate.

Procedures for obtaining artery waveform measurements are described in the device operator's manual. Participants will be instructed to fast and avoid caffeine, nicotine, anti-histamines and NSAIDS prior to study visits.

Blood pressure: Blood pressure will be assessed during artery elasticity waveform measures, and estimates will also be ascertained in triplicate.

Laboratory Tests: At each study visit, a peripheral blood draw (<50ml) will be performed by a study investigator or RN. Samples will be de-identified and labeled with a study ID number. In addition to toxicity labs (above), HIV RNA level, CD4+ T cell count and a fasting lipid panel (total cholesterol, LDLc, HDLc, and triglycerides) will be measured through HCMC clinical lab. Serologies for Hepatitis B and C will also be measured at the baseline visit only. Blood tubes for clinical tests will be immediately sent to HCMC clinical labs for processing. The following specimens will be processed and stored for biomarker assays:

- i. Citrated plasma: 10cc cyan blue

- ii. Plasma (EDTA): 10cc lavender
- iii. Plasma with heparin: 4cc green
- iv. Serum: 4cc yellow
- v. Platelet free plasma (CDAT): 4cc light-blue

Blood specimens for future biomarker analyses will be centrifuge blood at 2500 X g for 15 minutes (for a total of >30,000 g-minute spin) in a refrigerated centrifuge at 4°C. Before aliquoting, pre-label the 0.5cc storage vials. Using a transfer pipette and following aseptic techniques, immediately remove as much plasma as possible without disturbing the red cell layer. Transfer 0.5cc of plasma to each of the pre-labeled transport vials. Screw caps on tightly. Do not tape the caps on. Immediately freeze the vials in an upright position (at -80°C)

Citrated Plasma samples must be obtained without trauma (e.g. multiple sticks, patting venipuncture site, placing tourniquet on too tightly or for too long). This should be a Morning-Fasting (at least 8 hours, no food or drink except water) sample collected. Fill citrated plasma tube prior to obtaining any other labs, but after discarding a single tube with no additive (red-top). After collecting the participant's blood using 3.2% sodium citrate (light blue top) tube, gently invert the tube no more than 5 times to mix the blood and additive. Place filled citrate tube on wet ice and centrifuge within 30 minutes. Visually inspect sample. If a clot is present do not use the sample. The participant will need to have the sample re-drawn.

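### FRS outcome comes from an online calculator of unstated precision; if whole percents are recorded, rounding adds avoidable noise at the low eligible scores

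*Combined protocol and SAP*

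**What the plan says.** All references are to the combined protocol and SAP.

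- Section 2.2 lists among the primary outcomes: "Changes in Framingham risk score (FRS), including serum cholesterol levels and blood pressure". Section 4 plans to compare mean changes at 4 months for each drug against its placebo. It does not say whether the change is absolute, relative or on a log scale.
- Section 2.6 gives the source of the score: "Framingham 10-year risk score will be calculated using an NHLBI online algorithm", "after entering age, gender, smoking status, TC, HDLc, systolic BP and use of a BP lowering medication". The number of decimals returned or recorded is not stated, and there is no plan to compute the score from the equation itself.
- Section 2.1 admits scores from 3% and excludes those above 20%. Section 2.3 explains that the lower cut-off "eliminates the participants at very low risk for CVD", so low scores are admitted by design.
- Section 2.5 sizes the trial: "With a total sample size of 40 patients (20 per group for comparison of each drug intervention"), where a 0.9 SD "difference in 10-year Framingham risk score from each drug can be detected with 80% power at the 0.05 (2-sided) level of significance". For the variability, "the estimated SD based on 11,702 participants was 0.20", which the section treats as about 20% relative, making the target an 18% relative change. It illustrates this with a fall from 8% to 6.5%.

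**The concern.** A score that starts at 3% leaves little room for coarse recording. An 18% fall is 0.54 points at a score of 3% and 0.90 points at 5%. If scores are held as whole percents, both falls are smaller than one step. A participant at a true 3.0% who falls 18%, to 2.46%, would be recorded as going from 3% to 2%. One who falls 16%, to 2.52%, would be recorded as unchanged.

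The rounding error enters at both readings of each change and is relatively largest at the low scores that the design deliberately admits. It would widen the error of both drug comparisons on the only powered outcome. The sample size has no slack to absorb this: 40 participants give just about 80% power, and no allowance for dropout is stated. The loss would also be avoidable, because the score is a function of inputs the study already collects.

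**Working it through.** **Inputs.** From Section 2.5: 20 per group, SD 0.20, effect 0.18 (0.9 SD), two-sided 0.05, 80% power. From Section 2.1: eligible scores of 3% to 20%. Assumption, not in the documents: both readings are rounded to whole percents.

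**Step 1: reproduce the plan.** Normal approximation: 0.9 × √(20/2) − 1.96 = 0.886, which gives power 81.2%, and 20 per group suffice for 80%. The two-sample t-test gives 79.2%. The stated 80% is reproduced.

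**Step 2: size of one step.** One point divided by the score is 33% at 3, 25% at 4, 20% at 5, 16.7% at 6, 12.5% at 8 and 5% at 20. It equals 18% at 1/0.18 = 5.6. So a step is at least as large as the target effect at whole scores of 3 to 5, and smaller from 6 up.

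**Step 3: added noise if everyone were at one score.** Rounding variance is about 1/12 per reading, so 2/12 per change, an SD of √(2/12) = 0.408 points. Dividing by the score and combining with 0.20 gives the total SD. At a score of 3, for example: 0.408/3 = 0.136, and √(0.20² + 0.136²) = 0.242.

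| Score | Rounding SD | Total SD | t-test power for 18% | Total N for 80% (normal) |
|---|---|---|---|---|
| unrounded | 0 | 0.200 | 79.2% | 40 |
| 3% | 0.136 | 0.242 | 63.1% | 58 |
| 4% | 0.102 | 0.225 | 69.5% | 50 |
| 5% | 0.082 | 0.216 | 72.8% | 46 |
| 8% | 0.051 | 0.206 | 76.7% | 42 |

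**Step 4: a mix of scores.** The documents give no baseline distribution, so I take uniform spreads, starting at 2.5% because that is the lowest true value that would be recorded as 3%. Power is simulated for 20 v 20.

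| Baseline spread | Relative change: unrounded → rounded | Absolute change: unrounded → rounded |
|---|---|---|
| 2.5 to 6.5% | 79–80% → 70.9% | 76.0% → 69.0% |
| 2.5 to 10% | 79–80% → 73.4% | 73.5% → 69.9% |
| 2.5 to about 20% | 79–80% → 76.5% | 70.2% → 69.2% |

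A separate simulation of log change agrees: 79% falls to 65% for scores of 3–4%, 69% for 3–6%, 73% for 3–10%, 76% for 3–20% and 78% for 10–20%. On the absolute scale, too, a range confined to the lowest scores loses more than the table shows.

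**Step 5: one decimal instead.** At a score of 3 the rounding SD is 0.0408/3 = 0.014, the total SD is 0.2005 and power is 79.0%. The loss disappears.

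**The case against.** The strongest objection is that the premise is not in the documents. A reader might infer that the calculator returns whole percents because most scores in the protocol are written that way. The documents do not support that inference. The 3% is a cut-off. The 5% in Section 2.3 is an approximate risk after an adjustment for ART exposure, not a calculator output. The one-patient example in Section 2.5 (8% to 5%) does not match its own stated 25%, since 3/8 is 37.5%. The figure that bears most directly on precision, 6.5%, has a decimal. The examples do not settle the matter either way. This stands, and it makes the point conditional.

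A reader might also infer that the design's own illustration could never be observed: "Thus a change in Framingham risk of 8% to 6.5% would be" an improvement of more than 18%. That is too strong. The analysis compares mean changes, and a mean of whole-number scores can be 6.5.

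Nor is rounding a bias. Each reading is off by at most half a step in either direction, and the errors largely average out over 20 participants, leaving a less precise estimate.

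Three more limits stand. The SD of 0.20 may already contain some rounding, in which case part of the loss is already counted. Cholesterol and blood pressure, named within the same primary outcome, are unaffected. This is also a pilot, and Section 4 bases future sample sizes on arterial elasticity and biomarkers rather than FRS.

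The objection does not remove the gap: the precision is unstated, and a better calculation is available from the same data.

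**Conclusion.** The point holds in a conditional and fairly small form. Section 2.6 leaves the precision of the only powered outcome open. If whole percents are returned or recorded, the cost in power for an 18% relative change is:

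- about 3 points if baselines spread evenly over the eligible range;
- about 6 points if most are below 10%, and 8 to 9 if most are below 6.5%;
- 16 points only if all 40 participants are at 3%.

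On the absolute scale the corresponding spreads lose about 1 to 7 points. With one decimal the loss is negligible.

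These figures rest on three things the documents do not give: the recorded precision, the baseline mix and the scale of change. They also assume that the SD of 0.20 is free of rounding. It would be wrong to read the 63% power at a score of 3% as the trial's expected power, since that is the extreme case. The change is still worth making, because it costs almost nothing and makes the unknown precision irrelevant to the outcome.

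**What to change.** In Section 2.6, keep the online calculator for screening eligibility. For the outcome, state that FRS at baseline, month 1 and month 4 will be computed from the recorded inputs (age, sex, smoking status, TC, HDLc, systolic BP and BP-lowering medication) by one fixed program of the same Framingham equation, keeping unrounded values. Name the version of the equation, and confirm that every input is stored for each visit. Say that screening lipids serve as baseline values where they are not repeated, as the visit table in Section 2.4 allows. In Section 4, state the scale on which change is analysed.

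The cost is a short script and no new data. There is one small downside: a participant's screening score and analysis score may differ slightly, including near the 3% threshold. The text should therefore say that eligibility rests on the screening score and is not revisited. A fixed program also removes repeated entry into a website and any reliance on that site staying unchanged, although nothing in the documents suggests that it would change.
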